Repetitive transcranial magnetic stimulation (rTMS) is a painless and non-invasive neuromodulation technique. It can not only regulate nerve excitability and cortical function, but also modulate the activity of individual neurons [13], and it has been widely used in the treatment of a wide range of neuropsychiatric disorders. Studies have shown that cytokines (such as IL-1β, IL-6, and TNF-α) play a significant role in the pathophysiology of cognitive dysfunction. Moreover, rTMS has shown potential in regulating cognitive function by targeting the neuroinflammatory pathways associated with postoperative cognitive dysfunction (POCD). Recent studies exploring the effects of rTMS on inflammatory markers (such as IL-6 and TNF-α) also support its potential in alleviating neuroinflammation [14–16]. We hypothesize that, compared with sham rTMS and standardized perioperative management, perioperative left DLPFC rTMS will improve early postoperative cognition and attenuate perioperative increases in inflammatory biomarkers (IL-1β, IL-6, TNF-α, HMGB1). Accordingly, we designed a randomized, sham-controlled trial to test whether perioperative rTMS can improve cognition and modulate inflammatory responses after TKA.

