#### Secondary outcomes (five-element specification)

MoCA total score—measurement: total score (0–30); metric: change from baseline; aggregation: mean (SD) and mean difference (95% CI) from linear mixed models; time points: preoperative day six, preoperative day one, postoperative day three, postoperative day seven.

Digit Span Test (DST) (forward/backward)—measurement per standard DST; metric: value and change; aggregation: mean (SD) and mean difference; time points: preoperative day six, preoperative day one, postoperative day three, postoperative day seven.

Digit Symbol Substitution Test (DSST)—measurement: number correct in 90 s; metric: value and change; aggregation: mean (SD) and mean difference; time points: preoperative day six, preoperative day one, postoperative day three, postoperative day seven.

Trail Making Test (TMT)—measurement: time to completion (s); metric: value and change; aggregation: mean (SD); if skewed, median (IQR) and Hodges–Lehmann difference (pre-specified); time points: preoperative day six, preoperative day one, postoperative day three, postoperative day seven.

Delayed Story Recall (DSR)—measurement: story recall points; metric: value and change; aggregation: mean (SD) and mean difference; time points: preoperative day six, preoperative day one, postoperative day three, postoperative day seven.

Inflammatory markers (IL-1β, IL-6, TNF-α, HMGB1)—measurement: serum ELISA (pg/mL); metric: log-change from baseline; aggregation: geometric mean ratio (ANCOVA, baseline-adjusted) (or mean difference if normal); time points: preoperative day six, preoperative day one, postoperative day three, postoperative day seven.

All time points conform to the pre-specified SPIRIT schedule (preoperative day six, preoperative day one, postoperative day three, postoperative day seven); statistical baseline is defined as pre-op day 1 for all change analyses.

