### Participant timeline {13}

Following enrollment, each outcome indicator will be assessed at four time points: before the rTMS intervention (on preoperative day six), after the completion of the rTMS intervention (on preoperative day one), on postoperative day three, and on postoperative day seven. The schedule of enrollment, interventions, and assessments is summarized in the Standard Protocol Items: Recommendations for Interventional Trials (SPIRIT) figure.

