### Statistical methods

#### Statistical methods for primary and secondary outcomes {20a}

Analyses will follow intention-to-treat. Primary endpoint (POCD at postoperative day seven) will be compared between groups using log-binomial regression to estimate risk ratios (95% CI), adjusted for age, sex, education, and baseline MoCA; logistic regression will be used if convergence issues arise. A supportive analysis will model POCD trajectories at postoperative day three and postoperative day seven using generalized estimating equations with a log link.

Continuous secondary outcomes (MoCA total, DST, DSST, TMT, DSR) will be analyzed using linear mixed-effects models (fixed effects for group, time, and group × time; random intercept for participant), adjusting for baseline. For TMT, if residuals are markedly non-normal, we will report median (IQR) and between-group Hodges–Lehmann differences as pre-specified sensitivity analyses. Inflammatory markers will be log-transformed and analyzed using ANCOVA at each post-op time point with baseline adjustment; results will be back-transformed as geometric mean ratios (95% CI). Missing data will be handled under a missing-at-random assumption via maximum likelihood; multiple imputation (*m* = 20) will be a sensitivity analysis. Multiplicity across secondary outcomes will be controlled by the Benjamini–Hochberg procedure (false discovery rate 5%).

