### Methods in analysis to handle protocol non-adherence and any statistical methods to handle missing data {20c}

Analyses will follow the intention-to-treat principle, retaining all randomized participants in their allocated groups. To minimize loss to follow-up, we will employ proactive retention strategies (appointment reminders, flexible assessment windows, and phone/text follow-ups). For the primary endpoint and other repeated continuous outcomes, linear mixed-effects models will be estimated under a missing-at-random assumption using maximum likelihood; results will be stress-tested by prespecified sensitivity analyses including multiple imputation (*m* = 20) and a conservative worst-case scenario. Participants who deviate from the intervention protocol will remain in the ITT analysis; per-protocol/sensitivity analyses may be reported descriptively. We will not replace randomized participants; if attrition exceeds the prespecified allowance and materially threatens power, the TSC may, on DSMB advice and blinded aggregate information, approve extending recruitment to preserve target precision.

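### The marker analysis adjusts for a post-rTMS baseline, specifies no arm comparison at preoperative day one, and uses per-visit ANCOVAs that do not match the stated missing-data handling

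*Protocol article*

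**What the plan says.** All references are to the protocol article.

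- **Marker model, {20a}:** "Inflammatory markers will be log-transformed and analyzed using ANCOVA at each post-op time point with baseline adjustment". The cognitive scores are treated differently: "Continuous secondary outcomes (MoCA total, DST, DSST, TMT, DSR) will be analyzed using linear mixed-effects models".
- **Missing data, {20a}:** "Missing data will be handled under a missing-at-random assumption via maximum likelihood". No outcome is exempted, and multiple imputation (m = 20) is named as a sensitivity analysis.
- **Missing data, {20c}:** "For the primary endpoint and other repeated continuous outcomes, linear mixed-effects models will be estimated under a missing-at-random assumption using maximum likelihood". It adds that "results will be stress-tested by prespecified sensitivity analyses including multiple imputation", together with a worst-case scenario.
- **Marker outcome, {12}:** "metric: log-change from baseline; aggregation: geometric mean ratio (ANCOVA, baseline-adjusted) (or mean difference if normal); time points: preoperative day six, preoperative day one", followed by postoperative days three and seven. The section closes by fixing preoperative day one as the baseline for every change analysis.
- **Timing, {13}:** the first assessment, on preoperative day six, precedes the intervention. The other three come "after the completion of the rTMS intervention (on preoperative day one), on postoperative day three, and on postoperative day seven".
- **Intervention, {11a}:** five preoperative sessions and no postoperative rTMS.

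**The concern.** There are two problems, and the first matters more.

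**Baseline.** Preoperative day one is a post-treatment measurement. Under {20a} it enters the marker models only on the right-hand side. If rTMS lowers a marker before surgery, adjusting for that lowered value takes part of the effect out of the day-three and day-seven comparisons. The preoperative effect itself is not tested anywhere. Section {12} lists preoperative day one as a marker time point, but the log-change from a baseline taken on that day is zero by definition, so the plan lists a visit that it cannot analyse. The second objective in {7} concerns rTMS lowering inflammatory factors, so the markers are the main evidence for it.

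**Missing data.** A participant with a day-three sample and no day-seven sample drops out of the day-seven ANCOVA, and the day-three value is not used. A likelihood model fitted jointly to the visits would use it. Section {20a} therefore promises a property that its own marker model lacks. Section {20c} appears to prescribe a different model, since markers measured at four visits are repeated continuous outcomes.

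**Working it through.** The plan gives no figure for the marker analysis, so there is none to reproduce. It states no marker SD, between-visit correlation, effect size or dropout mechanism. Those are assumptions below, in SD units of the log marker.

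**Inputs from the plan:** 207 participants allocated 1:1:1, so 207/3 = 69 per arm; 10% anticipated attrition ({14}).

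**Step 1: effect of the baseline choice.** With equal variances and correlation ρ between preoperative day one and a later visit, the ANCOVA slope is ρ. The arm coefficient then estimates

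(effect at the later visit) − ρ × (effect at preoperative day one).

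For a constant effect δ this is δ(1 − ρ), so a fraction ρ is lost. With δ = −0.30:

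| ρ | Formula | Simulated, adjusted for preoperative day one | Simulated, adjusted for day six | Lost |
|---|---|---|---|---|
| 0.4 | −0.30 × 0.6 = −0.18 | −0.18 | −0.30 | 0.12 (40%) |
| 0.6 | −0.30 × 0.4 = −0.12 | −0.12 | −0.30 | 0.18 (60%) |
| 0.8 | −0.30 × 0.2 = −0.06 | −0.06 | −0.30 | 0.24 (80%) |

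(Simulation: 2,000 trials per row, no missing data.) A preoperative day-one comparison adjusted for day six recovers −0.30 in every row. If rTMS has no effect on the markers before surgery, the second term is zero and nothing is lost.

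**Step 2: effect of ignoring day three.** Two sets of simulations were run with 69 per arm.

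*Set A:* δ = −0.30 and preoperative day one as covariate. Day-seven loss depends on the day-three value in the comparator only. Overall loss is about 9%: about 6% in the active arm, hence about 2 × 9 − 6 = 12% in the comparator.

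| ρ | No missing data | Complete-case ANCOVA | Estimate using day three | Shift in ANCOVA |
|---|---|---|---|---|
| 0.4 | −0.176 | −0.151 | −0.184 | 0.025 |
| 0.6 | −0.121 | −0.084 | −0.116 | 0.037 |
| 0.8 | −0.061 | −0.040 | −0.061 | 0.021 |

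*Set B:* true day-seven effect −0.40 and a day-three to day-seven correlation of about 0.6.

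- Loss depends on day three in both arms (12% vs 8% to 15% vs 9%): ANCOVA gives −0.38 to −0.36, a shift of 0.02 to 0.04.
- Loss depends on day three in the comparator only (12% vs 6% to 16% vs 6%): ANCOVA gives −0.34 to −0.31, a shift of 0.06 to 0.09.
- The joint likelihood model gives −0.40 in all these cases.
- Under purely random loss both are unbiased, and the joint model's standard error is about 2% smaller.

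**Step 3: scale.** The ANCOVA standard error is √(2(1 − ρ²)/69), which is 0.167 at ρ = 0.2 and 0.147 at ρ = 0.5. A shift of 0.02 to 0.04 is therefore roughly an eighth to a quarter of one standard error. The baseline loss of 0.12 to 0.24 in Step 1 is several times larger.

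**Step 4: the texts side by side.** Section {20a} gives mixed models to five named cognitive scores and ANCOVA to the markers. Section {20c} gives mixed models to repeated continuous outcomes generally. Both cannot describe the main marker analysis.

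**The case against.** Several points on the other side stand.

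- A single-visit ANCOVA is itself a maximum-likelihood analysis, valid under missing at random when missingness depends only on arm and the baseline covariate. A reader might infer that the marker ANCOVA is incompatible with missing-at-random handling. That goes too far: what it cannot do is use day three for a missing day seven.
- A reader might also infer that marker results are complete-case throughout. Multiple imputation can use day-three values, and it is planned in both {20a} and {20c}, though only as a sensitivity analysis. The complete-case description fits the main analysis under {20a} alone.
- The largest missing-data figure, 15% to 23% of the effect (0.06/0.40 to 0.09/0.40), needs dropout tied to the day-three marker in the comparator only. Nothing in the plan says to expect that.
- It is tempting to claim that the preoperative day-one comparison would be more powerful than the postoperative ones. That holds only if a higher correlation is assumed for it. At a common value of 0.5 both have a detectable effect of 2.8 × 0.147 = 0.41 SD.
- The hypothesis in {6a} is that rTMS will "attenuate perioperative increases in inflammatory biomarkers (IL-1β, IL-6, TNF-α, HMGB1"), and postoperative tests speak to that. A preoperative test is partly an added analysis. This does not answer the baseline problem, because the postoperative comparisons are themselves weakened if rTMS has already acted by preoperative day one.
- Details of missing-data handling usually belong in an analysis plan, which is not shown. Two sections of the same article that name different models still need reconciling.

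**Conclusion.** The point holds in two parts of unequal weight.

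The larger part is the baseline. Sections {12} and {13} together make the one marker sample between rTMS and surgery a covariate, and no arm comparison is specified for it. Adjusting for it removes a fraction ρ of a constant effect, 40% to 80% at assumed correlations of 0.4 to 0.8. The loss is smaller if the preoperative effect is smaller than the later one, and nil if there is none. Changing ANCOVA to a mixed model while keeping that baseline would not cure this. Moving the baseline while still testing only postoperative visits would leave the preoperative comparison unmade.

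The smaller part is the mismatch between the per-visit ANCOVA and the likelihood handling in {20a} and {20c}. The resulting bias is about 0.02 to 0.04 SD in most of the assumed scenarios. It reaches 0.06 to 0.09 SD only in one set of assumptions with differential dropout.

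These are secondary outcomes, so the primary POCD analysis is not affected by this point. The change should still be made, before unblinding.

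**What to change.** Amend {12}, {20a} and {20c} so that they state the same marker analysis:

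- One repeated-measures likelihood model per log marker, with unstructured covariance and an arm-by-visit term.
- The preoperative day-six log value as covariate; preoperative day one, postoperative day three and postoperative day seven as responses.
- Geometric mean ratios with 95% confidence intervals at each visit, for active versus sham and active versus control. The day-one ratio is the effect of rTMS before surgery; the later two are the perioperative effect.
- In {12}, a marker-specific baseline of preoperative day six in place of preoperative day one.
- The added day-one tests included in the Benjamini–Hochberg family: 4 markers × 2 comparisons = 8.
- Multiple imputation kept as the sensitivity analysis.

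The cost is wording in three sections, a slightly larger false-discovery family, and a marker baseline that differs from the one now stated for all change analyses. All the samples are already scheduled, so no visits or blood draws are added.

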### Interim analyses and stopping guidelines {21b}

No formal interim efficacy analyses are planned. The rationale is threefold: (1) Endpoint timing and stability: The primary endpoint is the short-term change in cognitive performance at postoperative day 7; early looks would be based on small, potentially unstable samples and risk spurious findings without materially altering perioperative care. (2) Statistical operating characteristics: This is a three-arm trial with a modest total sample size. Alpha spending to accommodate interim efficacy looks would reduce the final power or require complex multiplicity control, which is not justified given the endpoint and effect-size uncertainty. (3) Bias minimization and trial integrity. Avoiding interim efficacy looks reduces operational and analytical bias risks (e.g., recruitment drift, performance bias) and preserves blinding and data quality.

Safety oversight and stopping for harm: An independent DSMB will review unblinded safety data six-monthly and ad hoc if signals emerge. The DSMB may recommend a temporary pause or early termination for safety if any pre-specified trigger is met, including: (1) any definite device-related seizure; (2) ≥ 2 rTMS-related SAEs or an rTMS-related SAE rate > 5% and exceeding the sham arm by ≥ 5 percentage points; (3) any unanticipated serious adverse device effect (USADE); or (4) clear excess of all-cause SAEs in the active rTMS arm versus sham at a scheduled review (conservative threshold). Final decisions will be made by the Sponsor/PI upon TSC advice.

### Methods for additional analyses (e.g., subgroup analyses) {20b}

There are no subgroup analyses planned.

### Methods in analysis to handle protocol non-adherence and any statistical methods to handle missing data {20c}

Analyses will follow the intention-to-treat principle, retaining all randomized participants in their allocated groups. To minimize loss to follow-up, we will employ proactive retention strategies (appointment reminders, flexible assessment windows, and phone/text follow-ups). For the primary endpoint and other repeated continuous outcomes, linear mixed-effects models will be estimated under a missing-at-random assumption using maximum likelihood; results will be stress-tested by prespecified sensitivity analyses including multiple imputation (*m* = 20) and a conservative worst-case scenario. Participants who deviate from the intervention protocol will remain in the ITT analysis; per-protocol/sensitivity analyses may be reported descriptively. We will not replace randomized participants; if attrition exceeds the prespecified allowance and materially threatens power, the TSC may, on DSMB advice and blinded aggregate information, approve extending recruitment to preserve target precision.

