### Outcomes {12}

#### Primary outcome (five-element specification)

Domain: POCD.

Specific measurement: MoCA administered at four scheduled assessments (preoperative day six, preoperative day one (baseline), postoperative day three, postoperative day seven) by a trained, blinded assessor.

Metric: Binary classification of POCD at each postoperative assessment. POCD is defined a priori as a ≥ 20% decline from baseline in ≥ 2 MoCA items (Newman criteria) [17].

Method of aggregation: The group-level proportion with POCD at postoperative day seven (primary time point); between-group effect expressed as risk ratio with 95% CI from a log-binomial model (logistic regression if non-convergent), adjusted for age, sex, education, and baseline MoCA.

Time point: postoperative day seven (primary); postoperative day three analyzed as supportive.

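### The missing-data section gives the primary endpoint a linear mixed model, which is incompatible with the binary day-seven POCD endpoint and its log-binomial analysis

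*Protocol article*

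**What the plan says.** All references are to the protocol article.

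- **Outcomes {12}, primary outcome.** The metric is "Binary classification of POCD at each postoperative assessment". Day seven is the primary time point and day three is supportive. The effect measure is a risk ratio.
- **Statistical methods {20a}.** The primary endpoint is to be "compared between groups using log-binomial regression to estimate risk ratios (95% CI), adjusted for age, sex, education, and baseline MoCA", with logistic regression if the model does not converge. Mixed models are reserved for other outcomes: "Continuous secondary outcomes (MoCA total, DST, DSST, TMT, DSR) will be analyzed using linear mixed-effects models". A GEE with a log link on days three and seven is supportive. On missing data: "Missing data will be handled under a missing-at-random assumption via maximum likelihood"; multiple imputation (m = 20) is a sensitivity analysis.
- **Non-adherence and missing data {20c}.** "For the primary endpoint and other repeated continuous outcomes, linear mixed-effects models will be estimated under a missing-at-random assumption using maximum likelihood". Multiple imputation and a worst-case analysis are listed as sensitivity analyses. The section also commits to intention-to-treat with everyone randomised kept in the assigned arm.
- **Interim analyses {21b}.** In passing: "The primary endpoint is the short-term change in cognitive performance at postoperative day 7".

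**The concern.** The word 'other' in the {20c} sentence classes the primary endpoint as a repeated continuous outcome. Under {12} and {20a} it is neither: it is one binary result at one visit.

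This matters because the mixed model is the only method that {20c} names for missing primary data outside the sensitivity analyses. A mixed model fitted by maximum likelihood can use a participant's earlier visits when the last one is missing. A regression on day-seven status alone cannot. If the log-binomial model is the primary analysis, the stated safeguard does not apply to it, and participants without a day-seven MoCA leave the main comparison.

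If {20c} is followed instead, the primary result becomes a difference in means rather than a risk ratio. It would then no longer match the sample size section {14}, which is built on a 15-percentage-point difference in proportions. Leaving both instructions in place also leaves room to choose between two primary models after the data are seen.

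**Working it through.** **1. The instructions side by side**

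| | {12} and {20a} | {20c} |
|---|---|---|
| Type of endpoint | binary | continuous |
| Visits in the primary model | day seven only | repeated |
| Model | log-binomial, logistic as fallback | linear mixed-effects |
| Effect | risk ratio | mean difference |

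No other section reconciles the two columns.

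**2. How many participants are affected**

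Inputs from {14}: 186 evaluable, 10% attrition, 207 planned, allocation 1:1:1. The attrition step reproduces: 186 / 0.90 = 206.7, rounded up to 207. The allowance is 207 − 186 = 21 participants, or 69 − 62 = 7 per arm. The 186 is taken as given; nothing here depends on how it was derived.

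**3. Why maximum likelihood alone does not recover them**

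In a one-visit binary model, a participant with outcome probability p and an unobserved outcome contributes p + (1 − p) = 1 to the likelihood. That factor carries no information, and day-three status does not enter the model.

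**4. Illustration within one arm** (the POCD split and dropout rates are assumptions; the 40% is the rate in {14})

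Half the arm has POCD on day three. Day-seven POCD occurs in 70% of those and in 10% of the rest.

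- True rate: 0.5 × 0.70 + 0.5 × 0.10 = 40.0%.
- Dropout 20% with day-three POCD, 5% without: (0.5 × 0.80 × 0.70 + 0.5 × 0.95 × 0.10) / (0.5 × 0.80 + 0.5 × 0.95) = 0.3275 / 0.875 = 37.4%.
- Dropout 5% in both groups: 0.38 / 0.95 = 40.0%.

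If one arm follows the first pattern and the other the second, the difference is off by 2.6 points. If both follow the first pattern with equal POCD rates, both read 37.4% and the difference is unbiased. Overall losses here are 12.5% and 5%, a mean of 8.75%, slightly under the planned 10%.

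**5. The same check at the design effect** (25% v 40%, true risk ratio 0.25 / 0.40 = 0.625)

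Assume day-three POCD in 80% of those with day-seven POCD and in 25% of those without. The joint proportions (both days, day seven only, day three only, neither) are 0.20, 0.05, 0.1875, 0.5625 in the active arm and 0.32, 0.08, 0.15, 0.45 in the control arm. Dropout is given as with / without day-three POCD.

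| Active dropout | Control dropout | Active observed | Control observed | Risk ratio |
|---|---|---|---|---|
| 18% / 5% | 18% / 5% | 0.2115 / 0.8996 = 0.235 | 0.3384 / 0.8889 = 0.381 | 0.62 |
| 22% / 4% | 10% / 10% | 0.2040 / 0.8903 = 0.229 | 0.400 | 0.57 |
| 5% / 12% | 18% / 4% | 0.2340 / 0.9071 = 0.258 | 0.3392 / 0.8942 = 0.379 | 0.68 |

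Because dropout here depends only on arm and day-three status, an estimate that uses day three within arm returns 0.625 in every row.

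**6. Outer limits**

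Take 7 missing per arm and, as the nearest whole numbers to the design rates, 16/62 v 25/62 observed. The observed risk ratio is 0.64. Counting all missing as POCD gives 23/32 = 0.72. Worst case for active is 23/25 = 0.92, and best case is 16/32 = 0.50.

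**The case against.** A reader might infer that the protocol plans a complete-case primary analysis and thereby breaks its intention-to-treat commitment. The text does not say so. Dropping these participants follows only if the log-binomial model governs and nothing is added to it, and an analysis plan that is not shown could add something.

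A reader might also infer that the missing-at-random claim is empty. It is not. The adjusted log-binomial fit to observed outcomes is valid when missingness depends only on arm, age, sex, education and baseline MoCA, which is a form of missing at random. What it lacks is the day-three information.

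Nor is missingness ignored. Imputation and a worst-case analysis are prespecified, and the supportive GEE includes people with only a day-three result.

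The bias figures rest on assumed dropout that depends on day-three status, and the larger ones need that pattern to differ by arm; with the same pattern in both arms, the risk ratio in step 5 moves only from 0.625 to 0.62. Imputation restores the truth there because the examples are built that way. It would do little for participants lost before day three, and would not repair missingness driven by unobserved day-seven status.

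Finally, the {21b} wording might be read as a second, continuous primary endpoint. POCD is itself defined as a decline from baseline, so this is loose phrasing in a rationale for having no interim analysis.

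All of this stands and limits the consequence. None of it reconciles {20c} with {12} and {20a}: the contradiction is in what the article states, not in what it leaves out.

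**Conclusion.** The contradiction is certain. {20c} names a model for the primary endpoint that cannot be the primary model fixed in {12} and {20a}.

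The consequence is conditional. If the log-binomial model governs as written, about 21 of 207 participants contribute nothing at the planned attrition, which sits badly with the commitment to keep everyone randomised. Whether bias follows depends on the dropout mechanism. There is none if missingness depends only on arm and the model covariates. Under the assumed patterns it is 2.6 points on one arm's rate, or a risk ratio of 0.57 to 0.68 against a true 0.625 when dropout differs by arm. These are illustrations, not forecasts. The documents do not support the stronger statements that the primary analysis is planned as complete-case or that missing data go unaddressed. The point should be corrected, but it does not by itself undermine the trial.

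**What to change.** - **{20c}:** delete the primary endpoint from the linear mixed model sentence, so that it covers the continuous secondary outcomes only.
- **{20a} and {20c} together:** state that missing day-seven POCD is handled in the primary analysis by the multiple imputation already planned (m = 20). The imputation model uses arm, age, sex, education, baseline MoCA and the other earlier MoCA data including day three. The log-binomial model is then fitted in each imputed set and the results pooled. Both sections must change, since both now call imputation a sensitivity analysis. Imputing POCD status directly is enough; item-level imputation by arm, with about 69 participants each, is more demanding than needed.
- **Sensitivity analyses:** report the observed-case log-binomial analysis and the worst-case analysis. The latter covers what imputation under missing at random cannot.
- **Optional:** align the {21b} wording with binary POCD at day seven.

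The cost is a change of wording and a little more programming. No participant procedure changes. The amendment should be made before unblinding, so that the choice of primary model cannot depend on the results.
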